## Methods

### Study Design

This study combines the evaluation of the usability of the InCoPE-App with the effectiveness of the individualized exercise program concerning cognitive function, physical performance, and quality of life. Thus, a mixed methods design with different methodological components will be used. The evaluation of the usability and effectiveness of the InCoPE-App will be based on the use of the app for a duration of 18 weeks in a nursing home setting. This approach represents a field study and will be carried out as a cluster-randomized controlled trial in which the InCope-App will be used with people with dementia and the individualized, multidomain exercise program will be delivered by nursing assistants with the help of the app. The nursing homes will be cluster randomized, and each nursing assistant will subsequently recruit at least 2 people with dementia (see Figure 1).

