### Participants

To evaluate the InCoPE-App in terms of usability and effectiveness, 2 different study samples are required (see Figure 1). The first sample will include the future users of the InCoPE-App (ie, nursing assistants). To this end, initial contact will be established through the heads of care facilities in southwestern Germany who suggest potentially interested nursing assistants, who will subsequently receive detailed information about the aims and the content of the study. The following inclusion criteria must be fulfilled: (1) willingness to participate in the training to familiarize themselves with the InCoPE app, (2) command of the German language as the InCoPE-App is only available in German at this time, and (3) employment at the nursing home for at least 18 weeks. External employees (eg, physical therapists) will be excluded.

The second sample will include participants with primary dementia living in nursing homes. This sample will be drawn to evaluate usability and trends toward the effectiveness of the individualized exercise program as delivered by the InCoPE app. Participants in the second sample will be selected by nursing assistants. Before entering the study, written consent by participants or their legal guardians will be obtained. Prior to the intervention, a clearance certificate from the participant’s general practitioner will be collected, which will also include information about the dementia diagnosis and other pertinent information such as medication intake and comorbidities. Additional inclusion criteria are (1) Alzheimer disease, vascular dementia, or other primary dementia; (2) mild to moderate stage of dementia (Mini-Mental State Examination [MMSE]: 10-24); (3) age older than 65 years; and (4) walking ability of at least 10 meters with or without a walking aid. Exclusion criteria include (1) secondary dementia, (2) other severe cognitive impairments, (3) other severe neurological conditions, (4) other severe acute diseases, and (5) severe motor impairments.

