### Sample Size

The sample size for the number of nursing assistants who will evaluate the InCoPE-App with regard to usability was defined using a probabilistic model of problem discovery for formative user research [34]. We defined a sample size comprising 22 participants to have a 90% chance of observing with a probability of 0.1. In the second study phase, outcomes also include usability in addition to the effectiveness of the InCoPE-App with respect to adaptations in physical and cognitive performance in people with dementia. For this reason, each participant will recruit 2 appropriate residents with dementia in accordance with our inclusion and exclusion criteria. We anticipate that our calculated sample size (N=44: intervention group [IG], n=22; control group [CG], n=22) will be appropriate to examine potential trends toward effectiveness of the InCoPE-App.

This sample size allows detection of moderate effects calculated using an ANOVA with repeated measures for within and between interactions. The calculation of the sample size with G*Power version 3.1.9.2 (Heinrich Heine University of Dusseldorf, Germany [47]; effect size ηp² = 0.07, α error probability .05, power 0.95) resulted in 44 participants.

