### Randomization and Concealment

The residents with dementia recruited by nursing assistants will be allocated to either the CG or IG. This allocation will be performed by cluster randomization as it is not possible to blind participants, nursing assistants, or study personnel regarding group allocation. Participants in the CG will only receive conventional treatment such as individualized medication, standard care, or therapeutic applications for 18 weeks. Participants in the IG will receive the individualized exercise program in addition to conventional treatment. To ensure equal conventional treatment for the IG and CG during the intervention, it will be continuously documented.

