### Statistical Methods

All analyses will be performed using SPSS 27.0 (IBM Corp, Armonk, NY). Prior to analysis, plausibility (eg, considering range and distribution) will be checked to minimize errors. The quantitative analysis comprises the evaluation of the usability questionnaires, which will be analyzed with respect to the corresponding guidelines and will be compared with representative data.

The baseline values of physical and cognitive performance will be compared between IG and CG using chi-square tests for categorical data, Mann-Whitney *U* tests for nonparametric variables, and t tests for continuous and normally distributed parameters. Normal distribution will be checked with the Shapiro-Wilk test. Means and standard deviations will be calculated for normally distributed data, and medians and interpercentile ranges will be calculated for non-normally distributed data. A 2-factor ANOVA with repeated measurement will be used to identify treatment effects. In addition, 95% confidence intervals and partial Eta² will be calculated. The log events will be summarized and analyzed descriptively. Potential effects among subgroups based on varying physical or cognitive performance, gender, fear of falling, and logged events (completed training sessions, average duration of the training sessions) will be investigated using chi-square tests and *t* tests.

Qualitative content analysis of the field notes will be conducted [48]. The interviews will be fully transcribed and checked for accuracy. The entire coding process will be independently performed by 2 scientists. The transcripts will be reviewed to identify meaningful content-related aspects. These aspects will be systematically described using a category system. Research questions and interview guidelines will be consulted to deductively derive the main categories. Subcategories will be inductively developed based on the findings (eg, by subsumption). The category system will be tested by 2 scientists who will independently test-code several parts of the qualitative material and subsequently adapt the categories and their definitions. The 2 coding systems will eventually be merged by consensual coding where consensus will be reached.

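### Residents are recruited by nursing assistants after their home is randomised, with no concealment step described, so entry to each arm can depend on the allocation; the two passages on order need reconciling

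*Protocol article*

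**What the plan says.** All references are to the protocol article.

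- **Order (Study Design):** "The nursing homes will be cluster randomized, and each nursing assistant will subsequently recruit at least 2 people with dementia".
- **Selector (Participants):** "Participants in the second sample will be selected by nursing assistants".
- **Allocation (Randomization and Concealment):** "The residents with dementia recruited by nursing assistants will be allocated to either the CG or IG". The section adds that cluster randomisation is used because "it is not possible to blind participants, nursing assistants, or study personnel regarding group allocation". Despite its heading, it describes no concealment: no list of residents fixed beforehand, no recruiter unaware of the arm, and no consent or baseline testing before disclosure.
- **Number chosen (Sample Size):** "each participant will recruit 2 appropriate residents with dementia in accordance with our inclusion and exclusion criteria", for a total of 44 residents, 22 per arm.
- **Limits on choice (Participants):** primary dementia, "mild to moderate stage of dementia (Mini-Mental State Examination [MMSE]: 10-24"), age over 65, ability to walk 10 m, five exclusions, written consent by the resident or guardian, and clearance by the general practitioner.
- **Analysis (Statistical Methods):** "The baseline values of physical and cognitive performance will be compared between IG and CG using chi-square tests for categorical data", with other tests for other data types. Then "A 2-factor ANOVA with repeated measurement will be used to identify treatment effects". No adjustment for baseline differences is named.

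**The concern.** In a cluster-randomised trial, randomising the homes balances the homes in expectation. It balances the residents only if the people who enter them do so without regard to the arm. If the assistant knows the arm when choosing, the residents can differ systematically between arms even though the homes were randomised properly.

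The task that follows selection differs between arms. An intervention resident is trained for 60 minutes twice a week over 18 weeks, whereas a control resident receives conventional treatment only. An assistant who knows that training will follow has a reason to choose differently, for example by willingness to cooperate, which the listed baseline tests would not capture well.

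Baseline measurement is also exposed. Quality of life uses a caregiver-administered form, and assistants instruct and time the Timed Up & Go test through the app. If recruitment follows allocation, these baseline values may be recorded with the arm known. At stake is whether a group-by-time difference can be attributed to the exercise program.

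**Working it through.** **1. Order.** Study Design places recruitment after randomisation, and the adverb is explicit. Randomization and Concealment speaks of recruited residents who will be allocated. That could mean recruitment comes first, but the sentence gives no sequence and the allocation is still by cluster. The two sections can be read in opposite ways; only the first states an order.

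**2. Knowledge of the arm.** The article does not say that assistants know the arm when they select. It says they cannot be blinded, and it describes nothing that would keep the allocation from them until selection is complete.

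**3. Room for choice.** Each assistant needs about 2 residents. Eligibility spans MMSE 10 to 24, and several exclusions turn on the word severe without a threshold. The number of eligible residents per home is not given, so the real freedom of choice cannot be calculated. The criteria narrow it, but nothing fixes which eligible residents are taken.

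**4. Whether the analysis repairs it.** With two groups and two time points, the interaction in the repeated-measures ANOVA is a comparison of mean change. A constant difference in starting level cancels. A difference in expected change, through motivation, cooperation or rate of decline, does not.

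**5. The plan's own figure.** Inputs from Sample Size: partial eta squared 0.07, alpha 0.05, power 0.95, N = 44. The correlation between time points is not given; 0.5 is assumed here.
- f² = 0.07 / 0.93 = 0.0753
- λ = f² × N × 2 / (1 − 0.5) = 0.0753 × 44 × 4 = 13.2, with 1 and 42 degrees of freedom
- Power = 0.945, which agrees with the stated 0.95 to within rounding (0.95 is first passed at an even N of 46)

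This confirms the test and sample size used in step 6. It neither supports nor weakens the concern.

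**6. Illustration of size.** Suppose the program has no effect, but selection alone shifts mean change between arms by d standard deviations of change. With 22 per arm and clustering ignored, λ = d² × 44 / 4 = 11d², again with 1 and 42 degrees of freedom.

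| Assumed d | λ | Rejection rate of the 5% test |
|---|---|---|
| 0 | 0 | 5% |
| 0.1 | 0.11 | 6.2% |
| 0.2 | 0.44 | 9.9% |
| 0.3 | 0.99 | 16.3% |
| 0.5 | 2.75 | 36.7% |

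Every d above zero is an assumption. No value of it can be drawn from the documents.

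**7. Baseline tests as a check.** The same arithmetic applies to a t test of baseline values with 22 per arm: a true imbalance of 0.5 SD would be flagged only about 37% of the time. A non-significant baseline comparison would therefore be weak reassurance.

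**The case against.** The strongest reply is that the order is not settled. The Study Design sentence points to a participant flow figure that was not available in the text read, and Randomization and Concealment can be taken to mean recruitment first. Homes can also be randomised without the result being disclosed at once. If residents are in fact recruited before disclosure, only a wording conflict remains. This stands as a limit on certainty. It does not remove the need to reconcile the two sections, because the only explicit order in the text is the unfavourable one.

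The text also leaves open who recruits control residents. Sample Size has 22 assistants with 2 residents each, which gives 22 × 2 = 44, both arms together. Primary Outcomes has each assistant deliver the program to 2 people, while the intervention arm holds only 22. So it is not certain that control assistants choose control residents. That uncertainty stands too.

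A reader might infer that the choice is nearly unrestricted, or that the protection of randomisation is lost altogether. The documents do not support either. Diagnosis, MMSE range, walking ability, exclusions, consent and clearance all constrain entry, and the size of the eligible pool is unknown.

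A reader might also assume that the bias favours the intervention. The direction is not determined. Assistants could choose fitter residents or those thought most in need, and fitter residents may have less room to gain, for example on the balance score capped at 5.

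Finally, the article speaks partly of trends toward effectiveness. That tempers the claim to be made from the result, but effectiveness measures are listed as primary outcomes and a treatment effect is tested. Selection distorts a trend as much as it distorts a test.

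**Conclusion.** The point holds in this form: as written, which residents enter each arm can depend on the allocation, baseline measures may be taken with the arm known, and the planned analysis does not correct for selection on expected change. This rests on the explicit order in Study Design, the assistants' role as selectors, and the absence of any described concealment where blinding is said to be impossible. That assistants actually know the arm at selection or at baseline is an inference, not a statement in the article.

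The size of any bias is unknown. The rejection rates of about 10%, 16% and 37% are conditional on assumed shifts of 0.2, 0.3 and 0.5 SD in mean change, with 22 per arm and clustering ignored. They show that modest selection would matter at this sample size, not that it has occurred. The point is worth acting on because the remedy is cheap and this kind of bias cannot be reliably repaired in the analysis.

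**What to change.** Reconcile Study Design with Randomization and Concealment so that both state one order. In each home:

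1. Assistants list all eligible residents.
2. Where more are eligible than needed, residents are taken from the list in random order.
3. Consent and the general practitioner's clearance are obtained, and all baseline assessments are completed.
4. Only then does the research team disclose that home's allocation.

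The text should also say who recruits and tests the control residents, and the flow figure should match.

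Enrolment began in October 2021, so some homes may already have been allocated. For these, report the order in which allocation, selection and baseline testing took place, and state it as a limitation. A sensitivity analysis by recruitment order would carry little information with 44 residents and should not be relied on as the remedy.

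**Cost.** Revised wording and a short delay between baseline and disclosure. Because most tests run in the app, test-module training and tablet access are needed in both arms before allocation is revealed; exercise-module training can follow in intervention homes. No additional residents are required. Whether the extra training can be absorbed by existing staff is for the research team to judge, since the article gives no figures on this.

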**Figure 1 figure1:**
[figure not shown]
Flow of participants. InCoPE: Individualized Cognitive and Physical Exercise.

### Ethical Approval

The study is conducted in accordance with the Declaration of Helsinki. The study was approved by the Ethics Committee of the Karlsruhe Institute of Technology (Karlsruhe, Germany).

### Participants

To evaluate the InCoPE-App in terms of usability and effectiveness, 2 different study samples are required (see Figure 1). The first sample will include the future users of the InCoPE-App (ie, nursing assistants). To this end, initial contact will be established through the heads of care facilities in southwestern Germany who suggest potentially interested nursing assistants, who will subsequently receive detailed information about the aims and the content of the study. The following inclusion criteria must be fulfilled: (1) willingness to participate in the training to familiarize themselves with the InCoPE app, (2) command of the German language as the InCoPE-App is only available in German at this time, and (3) employment at the nursing home for at least 18 weeks. External employees (eg, physical therapists) will be excluded.

The second sample will include participants with primary dementia living in nursing homes. This sample will be drawn to evaluate usability and trends toward the effectiveness of the individualized exercise program as delivered by the InCoPE app. Participants in the second sample will be selected by nursing assistants. Before entering the study, written consent by participants or their legal guardians will be obtained. Prior to the intervention, a clearance certificate from the participant’s general practitioner will be collected, which will also include information about the dementia diagnosis and other pertinent information such as medication intake and comorbidities. Additional inclusion criteria are (1) Alzheimer disease, vascular dementia, or other primary dementia; (2) mild to moderate stage of dementia (Mini-Mental State Examination [MMSE]: 10-24); (3) age older than 65 years; and (4) walking ability of at least 10 meters with or without a walking aid. Exclusion criteria include (1) secondary dementia, (2) other severe cognitive impairments, (3) other severe neurological conditions, (4) other severe acute diseases, and (5) severe motor impairments.

### Intervention

The individualized exercise program for people with dementia is based on earlier work by this research group and includes a combination of cognitive and physical exercises [19]. The included exercises were further differentiated to ensure a higher degree of individualization following the idea of individualized medicine [20]. The individualized exercise program is embedded in the InCoPE-App, which will be utilized by nursing assistants. The InCoPE-App will be installed on a tablet device (Android), and nursing assistants will be trained in the appropriate use of the app in order to test and instruct people with dementia. The training comprises theoretical online modules for self-study (eg, theoretical basics of physical exercise with people with dementia, objective testing of physical and cognitive performance in people with dementia, first steps with the InCoPE-App) and 2 face-to-face meetings (between project members or research staff and nursing assistants) for the usage of the InCoPE-App. The InCoPE-App contains detailed photographic materials and descriptions to offer visual support in the execution of the proposed tests and exercises.

The tests assessing motor and cognitive performance included in the InCoPE-App are based on published recommendations and were used with people with dementia before [21,22]. On the basis of cluster analysis in a large sample of people with dementia who participated in our group’s previous randomized controlled trial [19], we identified 4 homogeneous subgroups of people with dementia [23] who were also considered when we designed the InCoPE-App: participants with (1) below-average motor and cognitive performance, (2) average cognitive performance and above-average motor performance, (3) above-average cognitive and motor performance, and (4) above-average cognitive performance and below-average motor performance. The initial testing of physical and cognitive performance included in the InCoPE-App will be used to determine whether an individual belongs to cluster 1, 2, 3, or 4. Testing will be repeated every 3 weeks during the 18-week intervention period to allow the InCoPE-App to regularly adjust the duration, intensity, and contents of the cognitive and physical exercises based on the individual’s needs. We anticipate that the desired physical and cognitive adaptation to the exercise program will be achieved by gradually increasing exercise difficulty and intensity (eg, number of repetitions).

For each individual, the content of the individualized exercise program will vary based on the cluster categorization. For example, a person in cluster 1 will receive recommendations to complete exercises that focus on increasing balance, mobility, and strength as well as cognitive stimulation. In contrast, a person in cluster 4 will likely undergo exercise with a more pronounced focus on balance, mobility, or strength regardless of the degree of cognitive stimulation. Furthermore, promotion of endurance is part of every training session. The differentiation of each exercise is regulated via several degrees of difficulty and intensity. Moreover, additional cognitive input is subdivided into 3 levels of difficulty. Training sessions will take place twice per week on nonconsecutive days for 60 minutes. These 60 minutes are divided into a ritualized warm-up, first combination of exercises, short break with ritualized exercises for balance, second combination of exercises, and cooldown. Pure training duration will be about 40 minutes. The ritualization of training sequences will give the people with dementia a sense of security.

### Outcomes

#### Primary Outcomes

The primary outcomes were defined along the overall aim to evaluate the usability and effectiveness of the individualized exercise program delivered via the InCoPE-App. In Table 1, the questionnaires and measures for usability, quality of life, and overall cognition as well as methods to evaluate executive function and physical performance are listed.

**Table 1 table1:** Primary outcomes.

Dimensions	Assessments	Pre	Post	Implemented in the InCoPE^a^-App
Overall usability	Post-Study System Usability Questionnaire (PSSUQ) version 3 [24]	No	Yes	No
Overall usability	ISONORM, a questionnaire that operationalizes the 7 criteria of EN ISO 9241-10 [25]	No	Yes	No
Perceived hedonic and pragmatic quality	AttrakDiff 2 [26]	No	Yes	No
Quality of life	German Quality of Life-Alzheimer’s Disease (QOL-AD) [27]	Yes	Yes	No
Global cognition	Mini-Mental State Examination Test (MMSE) [28]	Yes	Yes	Yes
Executive function	Digit span [29]	Yes	Yes	Yes
Mobility	Timed Up & Go (TUG) test [30]	Yes	Yes	Yes
Mobility	6-meter walking test (6MWT) [31]	Yes	Yes	Yes
Function and strength of lower limbs	Modified 30-second chair stand test (CST) [32]	Yes	Yes	Yes
Balance	Frailty and Injuries: Cooperative Studies of Intervention Techniques-subtest 4 (FICSIT-4) [33]	Yes	Yes	Yes

^a^InCoPE: Individualized Cognitive and Physical Exercise.

Each nursing assistant will use the app to deliver the individualized exercise program within the 18-week intervention to 2 people with dementia. The overall usability will be assessed after the intervention using the Post-Study System Usability Questionnaire (PSSUQ) [24]. The PSSUQ gives insight into user satisfaction with a system (eg, system usefulness, information quality, and interface quality). This questionnaire can be considered a useful tool for field studies [24]. We will use PSSUQ version 3, which is comprised of 19 items such as system usefulness, information quality, and interface quality rated on a 7-point Likert scale (1: strongly agree to 7: strongly disagree) [24,34]. Furthermore, usability will be assessed using the ISONORM questionnaire [25], which covers the implementation of the 7 defined criteria based on the International Ergonomics Standard DIN EN ISO 9241-110. This questionnaire operationalizes the 7 criteria of the EN ISO 9241-10 and was developed to evaluate software development [35]. The completion of the questionnaire takes 10 minutes, and bipolar statements from 35 items are assessed using a 7-point Likert scale (1: very negative to 7: very positive) [35]. The perceived hedonic and pragmatic quality of the InCoPE-App will be assessed using the AttrakDiff 2 questionnaire [26]. This questionnaire evaluates the participants’ perceptions of the InCoPE-App by means of semantic differentials.

Examination of the effects of the InCoPE-App on physical and cognitive performance in people with dementia will be determined based on the listed variables in Table 1. The primary outcomes will be assessed before and after the 18-week intervention. To assess quality of life, the 13-item caregiver-administered version of Quality of Life-Alzheimer’s Disease (QOL-AD) [27] will be applied. The QOL-AD is a valid and reliable tool (internal reliability, α=0.88-0.89; test-retest reliability for caregivers, 0.92) [27]. Global cognition will be assessed with the MMSE [28]. The questionnaire will be implemented in the InCoPE-App. The MMSE easily assesses 7 areas of cognitive function, with sufficient test-retest reliability (0.80-0.95) [28,36]. To assess executive function, the Digit Span Test [29] will be administered. The Digit Span Test consists of 2 parts: forward and backward. Participants will be asked to repeat a sequence of 3 to 9 digits forward and of 2 to 8 digits backward. The InCoPE-App will be used to document the given answers. The Digit Span is a reliable and valid test [37].

The Timed Up & Go (TUG) test will be conducted by asking participants to rise from a chair, walk 3 meters, turn around, and then go back and sit down again on the chair [30]. Nursing assistants will instruct participants while using the InCoPE-App to assess the time taken by each participant. Time is measured from the initial impulse to stand up until participants are seated again. Everyday walking aids are allowed. For the 6-meter walk test (6MWT) [31], participants will be asked to walk from one side of the room to the other side, where the distance of 6 meters will be marked using start and finish lines on the floor. When participants cross these lines, the time required to walk 6 meters will be measured using the InCoPE-App. In front of the starting line and behind the finish line, participants will have about 2 meters for acceleration and deceleration. If needed, participants are allowed to use their walking aids. Strength and function of lower limbs will be assessed using the modified 30-second chair stand test (30s CST). For the modified 30s CST, participants will be asked to stand up from a chair (height 46 centimeters, with armrests) as often as possible for 30 seconds. The modified version allows the use of armrests [32], which is essential for the majority of older adults with dementia to safely perform this test. While testing lower extremities, no walking aids are allowed. Static balance will be determined using the Frailty and Injuries: Cooperative Studies of Intervention Techniques- subtest 4 (FICSIT-4) [33], in which participants are asked to perform 4 different standing positions (Romberg, semitandem, tandem, and single leg) for 10 seconds without walking aids or other assistance. The FICSIT-4 performance is rated on a scale of 0 to 5 points. If participants cannot hold the first position for at least 3 seconds, a score of 0 is given. In contrast, participants receive a score of 5 if they are able to stand in the most difficult (ie, single leg) position for at least 10 seconds.

The chosen tests for physical performance are considered reliable tests in a geriatric setting. Among people with dementia, the intraclass correlation coefficients for test-retest reliability are 0.79-0.82 for FICSIT-4, 0.83-0.89 for 6MWT, 0.78-0.88 for the modified 30s CST, and 0.72-0.99 for the TUG test [38,39]. The 95% minimal detectable changes are 58.9%-71.1% for FICSIT-4, 31.6%-41.5% for 6MWT, 33.2%-45.7% for the modified 30s CST, and 15.8%-39.6% for the TUG test [38,39]. No information about content and construct validity is available in this setting.

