## Introduction

The COVID-19 pandemic has had drastic consequences for all areas of everyday life. In many nursing homes, routine processes had to be changed. Some activities and treatments were reduced or, in areas, canceled. Hygiene and safety measures (eg, no external exercise instructors, no group settings) and the increased workload for nursing assistants led to suspending physical exercise programs and activities, especially when delivered in a group setting. The potential consequences for nursing home residents include reduced general activity accompanied by decrease in cognitive function and physical performance and a considerable loss of an individual’s quality of life. Furthermore, these COVID-19–induced changes may also have an economic impact and may increase care expenses in the long term.

Dementia is present in up to 50% of nursing home residents [1]. The clinical symptoms of this neurodegenerative disease include, but are not restricted to, decreased cognitive skills and reduced physical performance (eg, balance and mobility) [2,3]. Many people with dementia experience a rapid progression of the disease [1]. Thus, people with dementia might be seriously affected by COVID-19–induced reduction of physical or mentally stimulating activities and similar treatments (eg, physiotherapy, ergo therapy, social interactions) in nursing homes.

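### Both primary mobility outcomes are defined only as completion times, so a resident who cannot do the test at week 18 has no value and would fall out of the planned pre-post analysis

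*Protocol article*

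**What the plan says.** Table 1 of the protocol article (Primary Outcomes) lists the Timed Up & Go and the 6-meter walk under mobility, and the text says: "The primary outcomes will be assessed before and after the 18-week intervention".

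The same section defines both tests as times:

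- Timed Up & Go: "Time is measured from the initial impulse to stand up until participants are seated again".
- 6-meter walk: "the time required to walk 6 meters will be measured using the InCoPE-App". Walking aids are permitted: "If needed, participants are allowed to use their walking aids".

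Neither test has a ceiling time, a zero or a category for a resident who cannot complete it. For balance (FICSIT-4) the section does set a worst value: "If participants cannot hold the first position for at least 3 seconds, a score of 0 is given".

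Entry requires "walking ability of at least 10 meters with or without a walking aid" (Participants), and severe motor impairment is an exclusion. The Introduction remarks: "Many people with dementia experience a rapid progression of the disease". The analysis is given in Statistical Methods: "A 2-factor ANOVA with repeated measurement will be used to identify treatment effects", run in SPSS 27.0.

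**The concern.** A time exists only for someone who finishes. The entry criterion secures a time at baseline but not 18 weeks later. A repeated-measures ANOVA on a pre and a post value uses only residents who have both. Taken together, a resident who has lost the ability to walk contributes nothing to either mobility outcome, although this is the worst mobility result possible.

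If the program helps residents keep walking, more of these losses fall in the control group. The comparison is then made among residents who stayed able, a group formed after allocation, and part of the benefit goes uncounted. With 22 residents per arm, a few such cases can matter.

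There is also a question of scale. Seconds stretch out at the slow end: a small fall in speed in a very slow walker adds many seconds. The times of residents close to losing the ability therefore dominate the variance.

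**Working it through.** **No figure in the plan settles this.** The documents give no rate of lost walking ability, no gait speed and no expected decline. The sizes below are assumptions shown as a range. The 6-meter walk was simulated; the Timed Up & Go was not.

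**Step 1. Power lost through missing pairs.** Inputs from Sample Size: partial eta squared 0.07, alpha 0.05, N = 44. Assumed: correlation 0.5 between the two measurements, which the article does not state.

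- f² = 0.07/0.93 = 0.0753
- λ = f² × N × 2/(1 − 0.5) = 0.0753 × 44 × 4 = 13.25, with 1 and 42 degrees of freedom
- Power = 0.945, close to the stated 0.95, so the plan's figure is reproduced to within two residents (N = 46 gives 0.953).

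With 42 complete pairs the power is 0.934, and with 40 it is 0.922. Lost pairs alone cost little.

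**Step 2. Shift in the estimated difference.** Assumed inputs:

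- baseline speed normal with SD 0.18 m/s and mean 0.5, 0.6 or 0.7 m/s, with everyone at or above 0.20 m/s at entry
- SD of change 0.12 m/s
- mean decline of 0.08 m/s in controls and none in the intervention group, so the true benefit is 0.08 m/s
- unable to do the test when the post speed falls below 0.20 m/s

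| Baseline mean (m/s) | Unable, control | Unable, intervention | Difference, finishers (m/s) | Difference, unable = 0 (m/s) |
|---|---|---|---|---|
| 0.5 | 11.8% | 5.2% | 0.072 | 0.087 |
| 0.6 | 5.9% | 2.4% | 0.075 | 0.084 |
| 0.7 | 2.4% | 0.9% | 0.078 | 0.082 |

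Shortfall among finishers against the assumed 0.08 m/s:

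- baseline 0.5: (0.080 − 0.072)/0.080 = 10%
- baseline 0.6: (0.080 − 0.075)/0.080 = 6%
- baseline 0.7: (0.080 − 0.078)/0.080 = 2.5%

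For the slowest sample, 22 × 0.118 + 22 × 0.052 = 3.7 residents would be missing, leaving about 40 pairs.

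**Step 3. Standardized effect by scale** (difference in mean change divided by the SD of change, same assumptions):

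| Baseline mean (m/s) | Seconds, finishers (as planned) | Speed, finishers | Speed, unable = 0 |
|---|---|---|---|
| 0.5 | 0.54 | 0.63 | 0.64 |
| 0.6 | 0.53 | 0.65 | 0.65 |
| 0.7 | 0.53 | 0.66 | 0.66 |

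Most of the gain in sensitivity comes from moving from seconds to speed. Scoring unable as 0 adds little to the standardized effect, because the spread grows with the difference: in the slowest scenario the control SD of change rises from about 0.11 to about 0.14 m/s. What the zero adds is that every resident who was tested or was unable stays in the comparison.

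**The case against.** The strongest reply is that a journal article describes timed tests in their usual unit, and that coding of non-performance may be set in a document not shown. It is true that the article never says unable residents are excluded; this is an inference. What stands against the reply is that the article itself chooses the scale and the model, and together they leave no place for the worst outcome. The point concerns how a primary outcome is defined as well as missing data.

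Several stronger readings are tempting and should not be drawn:

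- **That many residents will stop walking.** The Introduction's remark on rapid progression carries no rate or time frame. Entry is limited to mild to moderate dementia without severe motor impairment, and walking aids are allowed. The walk with its run-in and run-out takes about 6 + 2 + 2 = 10 m, the same as the entry minimum, but only a resident exactly at that minimum has no reserve.
- **That FICSIT-4 and the chair stand already score such a resident as worst.** FICSIT-4 gives 0 for failing to stand in the first position, not for inability to walk. Someone who cannot walk 6 m may still stand, or rise with armrests.
- **That the effect would be understated by 17-18%.** This compares 0.072 with 0.087, but the zero-scored estimate is itself above the assumed 0.08 m/s because it counts lost walking as a fall to 0. Against 0.08 the shortfall is 10% at most in these scenarios.
- **That it would be understated by 13-34%.** This appears if inability depends only on the size of the decline and 5-20% of controls become unable. The documents support neither assumption.

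It is also fair that the bias is toward no effect, and that 0.008 m/s is small beside a standard error of about 0.12 × √(2/22) = 0.036 m/s. Field notes and counts of completed testing periods (Secondary Outcomes) can reveal non-completion, but they supply no mobility value.

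**Conclusion.** The point holds in a limited form. As written, the two mobility outcomes have no value for a resident who cannot do the test at week 18, and the planned ANOVA would omit that resident. Under the assumed rates (about 2-12% unable in controls, 1-5% in the intervention group) the difference among finishers falls about 2-10% short of a true 0.08 m/s, toward no effect. The planned scale is also less sensitive: a standardized effect of about 0.53, against 0.64-0.66 for speed with unable scored 0.

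These sizes rest wholly on assumed speeds, decline and threshold. In a fitter sample the bias nearly vanishes, though the advantage of speed over seconds remains. The documents do not show that the trial will lose many residents in this way, or that a false claim of benefit would result. Two of the ten assessments in Table 1 are affected. Priority is low to moderate.

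**What to change.** Before any post-assessment data are examined:

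1. Analyse the 6-meter walk as gait speed, 6 m divided by the time, with 0 m/s for a resident unable to complete it.
2. Analyse the Timed Up & Go as the reciprocal of the time with 0 for unable, or by ranks with unable as worst.
3. Have the app record unable separately from refused and absent. The last two stay missing.
4. Report the number unable per arm, and keep seconds among finishers as a supporting result.

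The cost is one outcome definition and one reason code, with no extra tests or residents. The downsides are a less familiar unit and a wider spread of change (control SD about 0.14 instead of 0.11 m/s in the slowest scenario). Values gathered at 0 also sit less comfortably with an ANOVA, and ranking with unable as worst is the alternative if there are many. The rule should be fixed in advance, because a choice made after seeing who stopped walking could favour either arm.
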